#### Surgical site infection

2.5.3

It is defined as the occurrence of at least one of the following in the surgical incision within 30 days postoperatively: (1) purulent drainage from the deep incision, not originating from the organ/space of the surgical site; (2) spontaneous dehiscence of the deep incision or surgical opening by a surgeon due to infection, accompanied by at least one of the following: fever (>38 °C), localized pain, or tenderness; (3) evidence of abscess or other deep incision infection detected by direct examination, reoperation, histopathology, or imaging; (4) diagnosis of deep incision infection by the surgeon or attending physician (32).

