### Assessment of postoperative infection

2.5

Postoperative infections will be evaluated by an independent, professionally trained review panel, including attending or higher–level cardiac surgeons, ICU physicians, and infectious disease specialists. All adjudicators will remain blinded to patients' lactate exposure group assignment and TWA lactate values. Postoperative infections to be recorded include sepsis, pulmonary infection, surgical site infection, mediastinitis, and endocarditis. The frequency of postoperative infection assessment is shown in Table 1.

**Table 1 T1:** Schedule of data collection and measurement time points.

Outcome measure Time		Visit 1	Visit 2	Visit 3	Visit 4	Visit 5	Visit 6	Visit 7	Visit 8
		Presurgery	During operation	Postoperative day 1	Postoperative day 2	Postoperative day 3	Postoperative day 7	Postoperative day 14	Postoperative day 30
Enrollment	Eligibility screening	×							
	Informed consent	×							
	Demographic characteristics	×							
	Baseline measures	×							
	Preoperative comorbidities	×							
Intraoperative	Surgery-related variables		×						
	physiological and anesthesia-related		×						
Postoperative	laboratory indices			×					
	SIRS score			×					
	GCS score			×	×	×	×	×	×
	Sequential Organ Failure Assessment Score			×	×	×	×	×	×
	Postoperative infection			×	×	×	×	×	×
	Acute kidney injury				×		×		
	Liver injury					×			
	ICU length of stay			×	×	×	×	×	×
	Mechanical ventilation duration			×	×	×	×	×	×
	Postoperative Adverse Events	Safety outcomes will be assessed from admission through 30 days post-surgery							

SIRS score, systemic inflammatory response syndrome score; GCS score, glasgow coma scale score.

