#### Data quality control

2.11.4

All study personnel will receive standardized training before study initiation, covering data collection methods, standard definitions, and form-filling procedures. Regular onsite or remote monitoring will be conducted, with random case checks against original medical records to verify accuracy. Key variables (e.g., lactate levels, postoperative infection diagnoses) will undergo dual verification by two independent researchers.

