## Discussion

3

Postoperative infection after cardiac surgery with CPB is a common and serious complication, significantly increasing hospital stay, reoperation rates, and mortality (40, 41). Although prior studies have shown that lactate levels are associated with various adverse postoperative outcomes (42–44), research specifically examining the relationship between TWA lactate levels during CPB and multiple types of postoperative infection remains limited. This study aims to fill this gap. Compared with previous studies, the present study has notable innovations: lactate levels are assessed using TWA during CPB, a dynamic indicator that accounts for changes over time and better reflects overall lactate burden (45); in addition, various types of postoperative infections are clearly defined as outcomes, providing a more comprehensive and rigorous assessment.

This prospective cohort study will systematically record preoperative and intraoperative information at patient enrollment and follow up on postoperative infection events, ensuring data completeness and temporal consistency, which improves inference. Strict definitions for exposure and outcomes are used, with infection diagnoses based on internationally accepted standards and independently verified by study personnel and attending physicians, ensuring study rigor. Comprehensive covariates—including demographics, laboratory tests, and surgical factors—will be collected to minimize confounding and more reliably evaluate the independent association between lactate and infection. Additionally, this study incorporates a DAG to guide covariate selection and clarify the assumed causal structure between intraoperative lactate exposure and postoperative infection, thereby enhancing the transparency and reproducibility of covariate selection and model specification.

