Our study has several limitations. This is a single-center cohort study conducted at a large cardiovascular center. Variations in CPB management protocols and perioperative care practices may differ from those at other institutions. These differences could influence lactate levels as well as clinical outcomes, thereby limiting the generalizability of the study findings. Lactate is a dynamic variable, and using TWA during CPB may miss some peak values despite capturing overall exposure. Additionally, combining different outcomes may obscure differential associations between lactate and specific infection types. For example, lactate may have a stronger association with pneumonia (due to its effects on pulmonary microcirculation) and a weaker association with mediastinitis or wound infections (which are primarily related to surgical technique and dressing change frequency). Moreover, the 30-day follow-up window may not capture infections with delayed onset, particularly infective endocarditis, and may therefore underestimate the overall postoperative infectious burden. Accordingly, the findings of this study will primarily reflect the association between intraoperative TWA lactate and early postoperative infection.

If TWA lactate during CPB is found to be significantly associated with postoperative infection risk, it could serve as a potential early risk-stratification and intervention tool. Lactate monitoring is simple and cost-effective; elevated levels may prompt enhanced postoperative surveillance, optimized intraoperative management, and immunonutrition support, enabling early identification and intervention for high-risk patients. Future studies should consider large-scale, multicenter cohorts. Basic research should explore the biological mechanisms linking lactate levels and postoperative infection, including specific pathways of immune suppression and inflammatory responses. Finally, interventional studies should focus on methods to reduce lactate levels after CPB and whether lowering lactate can decrease postoperative infection rates, providing stronger evidence for clinical practice. This study aims to offer new biomarker combinations and decision-support tools for early warning and intervention of postoperative infection in cardiac surgery, ultimately improving patient outcomes and reducing healthcare costs.

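### Surgical site infection can be met by the treating doctor's diagnosis alone, and the protocol does not say that the blinded panel may reject it

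*Protocol article*

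**What the plan says.** Four places in the protocol article bear on who decides that a patient had an infection.

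- **Section 2.5, Assessment of postoperative infection:** "Postoperative infections will be evaluated by an independent, professionally trained review panel". Surgical site infection is among the infections listed there. On blinding: "All adjudicators will remain blinded to patients' lactate exposure group assignment and TWA lactate values".
- **Section 2.5.3, Surgical site infection:** "It is defined as the occurrence of at least one of the following in the surgical incision within 30 days postoperatively". Four items follow, and the last is "4) diagnosis of deep incision infection by the surgeon or attending physician".
- **Section 2.11.4, Data quality control:** "Key variables (e.g., lactate levels, postoperative infection diagnoses) will undergo dual verification by two independent researchers".
- **Section 3, Discussion:** diagnoses are "independently verified by study personnel and attending physicians".

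Section 2.8.1 makes surgical site infection one of the five infection types that form the primary outcome, so one such infection makes the patient an event.

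**The concern.** The exposure is a laboratory value measured in theatre, and the study has no randomisation. Its protection against detection bias is that whoever assigns the outcome does not know the exposure. Criterion 4 weakens that protection. Under the first three surgical site criteria there is a finding that a panel can look at: drainage, dehiscence or surgical opening with signs, or an abscess or other evidence on examination, reoperation, histology or imaging. Under criterion 4 the clinician's opinion is itself the criterion. A panel that applies the definition literally has nothing left to judge, and blinding the panel does not blind the opinion.

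The surgeon and the attending physician are not stated to be blinded. That they know something of the patient's lactate is an inference, but a reasonable one. The Introduction says that lactate is monitored routinely around surgery, and section 2.4 requires at least four measurements on bypass, with extra samples when lactate rises suddenly. A clinician who has seen high values may look harder at a wound or call a doubtful one infected. That error would run towards the study hypothesis.

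The other two statements on verification make it harder to rely on the panel. They name different people and do not mention blinding, and section 2.11.4 lists lactate levels and infection diagnoses together as items for the same kind of check.

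**Working it through.** **Step 1. Compare the passages on who decides.**

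| Place | Who | Blinding stated |
|---|---|---|
| Section 2.5 | Independent panel of cardiac surgeons, ICU physicians and infectious disease specialists | Yes, to exposure group and TWA lactate |
| Section 2.5.3, criterion 4 | Surgeon or attending physician | No |
| Section 2.11.4 | Two independent researchers, for lactate and for infection | No |
| Discussion | Study personnel and attending physicians | No |

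No section says whose decision is final. For pulmonary infection (section 2.5.1) and endocarditis (section 2.5.5) this matters less, because imaging, laboratory, culture or echocardiographic evidence is required. For criterion 4 it decides whether the patient is an event.

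**Step 2. Reproduce the plan's figure.** Section 2.3 gives 10.4% in the normal-lactate group, an odds ratio of 2.75, two-sided α 0.05 and power 0.9.

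- Odds in the high-lactate group: 2.75 × 0.104/0.896 = 0.3192, so the rate is 0.3192/1.3192 = 24.2%.
- n per group = [1.960 × √(2p̄(1−p̄)) + 1.282 × √(p₁(1−p₁) + p₂(1−p₂))]² / (p₂ − p₁)², with p₁ = 0.104, p₂ = 0.242 and p̄ = 0.173. This gives 155.9, rounded up to 156.

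The stated 156 per group is reproduced. The present point does not change it.

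**Step 3. Illustrate the size (assumed inputs).** The documents give no rate of diagnoses that rest on criterion 4 alone. Assume a true infection rate of 10.4% in both groups, hence no association. Let a fraction f of patients without infection receive an extra diagnosis. The observed rate is then p = 0.104 + 0.896 × f.

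- Unexposed, f = 1%: p = 0.1130, odds 0.1273.
- Exposed, f = 2%: p = 0.1219, odds 0.1388. Odds ratio 0.1388/0.1273 = 1.09.
- Exposed, f = 3%: p = 0.1309, odds 0.1506. Odds ratio 0.1506/0.1273 = 1.18.

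With 156 per group, an unadjusted two-sided 5% test (normal approximation) rejects in about 5.7% and 7.7% of such studies.

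**Step 4. Show the range.** If the excess falls in the exposed group only, added directly to 10.4%:

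| Excess (percentage points) | Odds ratio with no true effect | Rejection rate |
|---|---|---|
| 0 | 1.00 | 5.0% |
| 1 | 1.11 | 5.9% |
| 2 | 1.22 | 8.6% |
| 3 | 1.33 | 12.9% |
| 5 | 1.57 | 26.0% |

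The first rows are modest. The last needs an excess equal to about half the baseline infection rate (5/10.4 = 48%), which is a lot to ask of one criterion of one component.

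**The case against.** The best defence is that section 2.5 already gives the evaluation of infections, surgical site infection included, to a blinded panel, and that section 2.5.3 only supplies the definition the panel applies. The Discussion phrase may be a loose summary of that panel, which itself contains attending-level surgeons and physicians. Criterion 4 comes from a cited definition. The exposure is a calculated average split at 2.0 mmol/L, which ward staff are not said to have. And an article need not set out adjudication procedures in full.

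Much of this stands, and it limits the point in four ways.

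- A reader might infer that the panel is bypassed and that staff who know the exposure decide the primary outcome. The text does not say so: the panel keeps its role, and what is missing is its authority over criterion 4.
- A reader might cite the ICU handover in section 2.7 as proof that clinicians learn the lactate. Lactate is not among the handover items listed.
- A reader might take the Discussion remark that "elevated levels may prompt enhanced postoperative surveillance" as evidence of unequal surveillance in this study. It describes possible use if an association is found.
- Rules on the content of review packets, and on panel members who treated the patient, are matters for an adjudication charter. Their absence here is no finding.

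What does not stand is that the cited source settles the matter. A published definition may include a clinician's diagnosis, but that does not make the diagnosis blinded. Nor is this only detail left to a fuller document: the article itself states a criterion that suffices alone and three differing accounts of who checks infections.

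**Conclusion.** The point holds in a limited form. Followed as written, section 2.5.3 lets a diagnosis by clinicians who are not stated to be blinded satisfy one of five components of the primary outcome with no objective sign. The protocol does not say that the blinded panel may reject it, and section 2.11.4 and the Discussion name other verifiers. That clinicians know routine lactate values is probable rather than documented, and they may know neither the TWA nor the group.

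The size is unknown. The odds ratios of about 1.09 to 1.18 rest wholly on assumed rates of 1% against 2% to 3%, and are small beside the planning odds ratio of 2.75. They would matter most if the true association is weak, because the expected bias is in the same direction as the hypothesis. The change should be made because it is cheap and removes an avoidable doubt. There is no evidence that the result will be materially wrong without it.

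**What to change.** 1. In section 2.5.3, state that a diagnosis under criterion 4 triggers panel review and counts as an event only if the blinded panel confirms deep incisional infection from source evidence. This keeps the criterion as a way of finding cases. Requiring criterion 1, 2 or 3 as well would in effect delete part of the cited definition and is not needed.
2. In section 2.11.4 and the Discussion, say that the blinded panel of section 2.5 alone assigns the endpoint, and that the other checks concern data accuracy.
3. In section 2.5, extend the stated blinding from exposure group and TWA to all lactate values, including single, peak and postoperative ones.
4. Add a sensitivity analysis of the primary outcome that excludes events resting on criterion 4 alone. This requires recording which criterion each event met.

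The cost is wording in three sections, one recorded item, one extra analysis and a little more panel work. The panel already exists, and the sample size is unchanged. There may be a few fewer surgical site events, particularly after discharge, when follow-up is by telephone (section 2.11.1) and source evidence may be harder to obtain.

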#### Mediastinitis

2.5.4

It is defined as a wound infection involving the sternal bone within 30 days postoperatively, with or without involvement of the retrosternal space (33). Retrosternal involvement will be determined based on radiologic evidence (contrast-enhanced CT or MRI), supported by intraoperative findings or microbiological culture when available.

#### Infective endocarditis

2.5.5

It is defined as meeting both of the following criteria within 30 days postoperatively: (1) positive blood cultures for common pathogens of infective endocarditis (such as staphylococcus aureus and streptococcus viridans); (2) echocardiographic evidence of infective endocarditis (34).

### Covariates

2.6

To ensure appropriate confounder control and strengthen inference, a directed acyclic graph (DAG) and temporal sequence diagrams for variables were constructed based on prior clinical knowledge and published evidence (Figures 3, 4). These diagrams clarify the assumed causal pathways linking intraoperative TWA lactate to postoperative infection. The DAG identified the following minimal sufficient adjustment set: age, sex, BMI, lifestyles (including smoking and alcohol consumption), comorbidities, preoperative lactate, anesthesia factors, surgery and CPB factors (including surgery type, operation duration, CPB time, aortic cross-clamp time, and intraoperative body temperature). These variables are common causes of elevated lactate during cardiopulmonary bypass and of postoperative infection risk. Mediators include hepatic and renal dysfunction, lactate clearance, inflammatory response, and immunosuppression. ICU length of stay, hospital length of stay, time to extubation, and mortality are considered collider variables.

**Figure 3 F3:**

Temporal sequence of variables included in the causal framework.

**Figure 4 F4:**
[figure not shown]
Directed acyclic graph (DAG) illustrating the assumed causal structure between intraoperative TWA lactate (exposure) and postoperative infection (outcome). The exposure is represented by a green node with a triangle symbol. The outcome, postoperative infection, is shown as a blue node with a thick black vertical line. Other variables are represented as follows: blue nodes depict ancestors of the outcome, namely mediators; red nodes represent ancestors of both the exposure and outcome; pale grey nodes signify unobserved or latent variables; and darker grey nodes represent colliders. The definitions of TWA lactate and postoperative infection have been elaborated in the Methods section. Mediators located on the causal pathway between exposure and outcome, as well as colliders jointly caused by both exposure and outcome, will not be adjusted for to avoid overadjustment bias. The minimal adjustment set for this model is age, sex, BMI, lifestyle, comorbidities, preoperative lactate, anesthesia factors, and surgery and CPB factors.

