#### Demographics and baseline characteristics

2.6.1

Age (years), sex (male/female), BMI (kg/m^2^), smoking history (yes/no; defined as continuous or cumulative smoking for more than six months), alcohol consumption (yes/no; defined as drinking ≥1 time per month for ≥1 year), and NYHA functional class (I: patient has heart disease but no limitation of physical activity; ordinary physical activity does not cause undue fatigue, palpitations, dyspnea, or angina; II: slight limitation of physical activity due to heart disease; III: marked limitation of physical activity due to heart disease; IV: heart disease with symptoms of heart failure or angina at rest, any physical activity increases discomfort).

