#### Preoperative comorbidities

2.6.2

Hypertension (systolic BP ≥140 mmHg or diastolic BP ≥90 mmHg or taking antihypertensive drugs, yes/no), diabetes (fasting glucose ≥7.0 mmol/L, 2-hour postprandial glucose ≥11.1 mmol/L, random glucose ≥11.1 mmol/L, or taking antidiabetic drugs, yes/no), arrhythmias (including atrial arrhythmia, ventricular arrhythmia, atrioventricular block, yes/no), history of cerebrovascular disease (including cerebral infarction or hemorrhage, yes/no), hypoproteinemia (serum total protein <60 g/L or serum albumin <35 g/L, yes/no), pulmonary comorbidities (including chronic obstructive pulmonary disease, asthma, interstitial lung disease, pulmonary edema, yes/no), anemia (adult male <120 g/L, adult female <110 g/L, yes/no) and obesity (BMI ≥30 kg/m^2^, yes/no).

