#### Preoperative laboratory and functional indicators

2.6.3

Lactate level (mmol/L), platelet count (10⁹/L), hemoglobin (g/L), lymphocyte count (10⁹/L), neutrophil count (10⁹/L), monocyte count (10⁹/L), B-type natriuretic peptide (BNP, pg/mL), C-reactive protein (CRP, mg/L), left ventricular ejection fraction (LvEF, %), cardiac troponin I (CTnI, μg/L), myoglobin (Mb, μg/L), total bilirubin (*μ*mol/L), serum creatinine (μmol/L), alanine aminotransferase (U/L), aspartate aminotransferase (U/L), blood urea nitrogen (mmol/L), and preoperative blood glucose (mmol/L) within seven days before surgery.

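### The primary adjustment set holds no direct measure of preoperative cardiac or renal function, although both are collected before bypass, so residual confounding of the lactate odds ratio is likely

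*Protocol article*

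**What the plan says.** Section 2.6 (Covariates) calls the set sufficient: "The DAG identified the following minimal sufficient adjustment set: age, sex, BMI, lifestyles (including smoking and alcohol consumption), comorbidities, preoperative lactate, anesthesia factors", followed by surgery and bypass factors, namely surgery type, operation duration, bypass time, cross-clamp time and intraoperative temperature. The Figure 4 legend repeats it: "The minimal adjustment set for this model is age, sex, BMI, lifestyle, comorbidities, preoperative lactate, anesthesia factors, and surgery and CPB factors". Section 2.9 restricts adjustment in the primary logistic model to the common causes that the DAG identifies.

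Section 2.6.2 defines eight comorbidities. The list opens with "Hypertension (systolic BP ≥140 mmHg or diastolic BP ≥90 mmHg or taking antihypertensive drugs, yes/no" and goes on to diabetes, arrhythmias, cerebrovascular disease, hypoproteinemia, pulmonary disease (which includes pulmonary edema), anemia and obesity. Heart failure, low ejection fraction and chronic kidney disease are not among them.

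The direct measures stand elsewhere under the same Covariates heading. Section 2.6.1 records "and NYHA functional class (I: patient has heart disease but no limitation of physical activity" and the remaining classes up to IV. Section 2.6.3 records "left ventricular ejection fraction (LvEF, %), cardiac troponin I", together with BNP, serum creatinine and blood urea nitrogen, from the week before surgery.

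In the causal description, renal function appears only here: "Mediators include hepatic and renal dysfunction, lactate clearance, inflammatory response, and immunosuppression". The Figure 4 legend says of mediators and colliders that they "will not be adjusted for to avoid overadjustment bias".

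**The concern.** A patient with a poor ventricle or impaired kidneys may plausibly run a higher lactate on bypass and also be more prone to infection. If so, preoperative function is a common cause, which is the kind of variable that section 2.9 undertakes to adjust for. It is measured before the exposure, so the over-adjustment argument used for mediators does not apply to it. Yet an analyst who follows section 2.6 and the Figure 4 legend as written would leave it out.

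The Discussion says that the collected covariates will serve to minimize confounding and to evaluate an independent association. An upward bias would favour the study hypothesis. The set is stated explicitly and called sufficient, so this is a choice the plan has made and not a detail left to a later document. Adding terms after the data have been seen would be a post hoc repair.

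**Working it through.** **1. Is any direct measure in the set?**

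| Variable | Where collected | Before bypass? | In section 2.6 set or Figure 4 legend? | Brought in by section 2.6.2? |
|---|---|---|---|---|
| Ejection fraction | 2.6.3 | yes | no | no |
| NYHA class | 2.6.1 | yes | no | no |
| BNP | 2.6.3 | yes | no | no |
| Creatinine, urea nitrogen | 2.6.3 | yes | no | no |

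**2. What in the plan controls preoperative severity indirectly?** Within the set: preoperative lactate; arrhythmia, pulmonary edema, anemia and hypoproteinemia (through comorbidities); surgery type; and bypass and cross-clamp times. By restriction: section 2.2.2 excludes severe renal dysfunction, with examples that include creatinine >442 μmol/L, blood urea nitrogen >20 mmol/L and dialysis. It names no limit on ejection fraction or NYHA class. What remains open is the part of cardiac and renal function that these terms do not capture.

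**3. How large could the residual bias be?** The documents give no association of cardiac or renal function with lactate or infection, so all inputs here are assumptions.

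*Maximum bound, risk-ratio scale.* If the omitted factor is associated with both exposure and outcome by a risk ratio RR, given the covariates already adjusted for, the bounding factor is RR × RR / (2 × RR − 1).
- RR = 1.5: 2.25 / 2 = 1.125
- RR = 2.0: 4 / 3 = 1.333

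*Illustration, odds-ratio scale.* Assume a binary marker of poor function present in 20% of the low-lactate group and 30–50% of the high-lactate group, an infection odds ratio of 1.5–3 for the marker, and 9% risk in patients with neither marker nor high lactate.
- Worked case (marker odds ratio 2; 40% vs 20%; true lactate odds ratio 1.0): risk with the marker is 0.165. High-lactate risk = 0.4 × 0.165 + 0.6 × 0.09 = 0.120. Low-lactate risk = 0.2 × 0.165 + 0.8 × 0.09 = 0.105. The odds ratio without the marker is about 1.16.
- Over the whole range, a true odds ratio of 1.0 appears as 1.04–1.42, and a true 2.0 as 2.08–2.75.

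**4. Is there room in the model?** Section 2.3 reproduces: 10.4% and an odds ratio of 2.75 give 24.2% in the high-lactate group, and a pooled two-sided test at 90% power needs 156 per group. That calculation is unadjusted, so the covariate set does not affect it.
- Expected events in 312 patients under the design rates: 156 × (0.104 + 0.242) ≈ 54.
- If the overall rate is 10.4%: 312 × 0.104 ≈ 32.
- Parameters under an assumed coding: exposure 1, age 1, sex 1, BMI 1, smoking and alcohol 2, comorbidities 8, preoperative lactate 1, surgery type 4, operation, bypass and clamp times plus temperature 4, anesthesia duration 1; total 24.
- Events per parameter: 54 / 24 ≈ 2.2, or 32 / 24 ≈ 1.4 at the lower event count.
- With two terms added and none removed: 54 / 26 ≈ 2.1, or 32 / 26 ≈ 1.2. With two added and two removed, there is no change.

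**The case against.** The strongest reply is that much of preoperative severity is already covered. Preoperative lactate is a baseline measure of the exposure variable itself, so part of any path from poor function to bypass lactate is blocked. The other items in step 2 add to that, and the renal range is cut at its severe end. This stands. A reader might infer from the missing variables that the estimate is simply uncontrolled for how ill patients were before surgery; the documents do not support that.

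A reader might also infer that the plan treats preoperative creatinine as a mediator. It does not say so. The legend places mediators on the path from exposure to outcome, and section 2.8.2 defines postoperative kidney and liver injury as outcomes, so the mediator node can be read as postoperative. What stands is that section 2.6 does not say which is meant, and preoperative renal function has no other place in the causal description.

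The DAG image is not available here, and a measured variable can be unnecessary if its paths are blocked by others. This limits certainty about why the variables were left out. It does not change the set, which is stated in words in two places.

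Finally, the bias figures rest on assumed inputs and say nothing specific about this cohort. That stands too.

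**Conclusion.** The primary adjustment set contains no direct measure of preoperative cardiac or renal function, although such measures are collected and precede the exposure. Existing covariates and the eligibility criteria are partial controls, so the issue is residual confounding. An upward direction is probable only if poorer function raises both lactate and infection risk, which is a clinical judgement that the documents neither quantify nor rule out. The size cannot be derived from the documents. The 1.13-fold and 1.33-fold figures are maximum bounds under assumed associations, on the risk-ratio scale while the study reports odds ratios, and they apply after conditioning on the covariates already in the model. Confidence in the magnitude is low. The change is still worth making before analysis, because it is cheap and would be post hoc later.

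**What to change.** Add preoperative ejection fraction and creatinine to the primary adjustment set, each as one continuous term. NYHA class would take three indicators for its four levels, so ejection fraction is the more economical cardiac measure. In section 2.6 and Figure 4, word the mediator as postoperative hepatic and renal dysfunction.

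To keep the parameter count about constant, drop the obesity indicator, since BMI is already in the model. If anesthesia duration is one of the anesthesia factors (section 2.6 does not itemise them; section 2.11.1 lists it among the anesthesia-related parameters), also drop either it or operation duration, because the two overlap.

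The cost is wording only, as both variables are already collected. The downside is at most two extra parameters in a model that is already crowded, with roughly 32–54 expected events. The change does not cure that crowding and, with the two removals, does not add to it.
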